#### Primary Outcomes

The primary aim of this study is to assess whether the Activ4Brain program leads to improved cognitive function in cognitively healthy older people. We will focus on measures from the cognitive assessment protocol associated with 5 cognitive domains: executive function, working memory, episodic memory, sustained attention, and processing speed. These are our primary outcomes.

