### Cognitive Assessment

General cognitive function is assessed using standardized neuropsychological tests (Table 3). Participants are screened for the presence of objective cognitive impairment using the Addenbrooke’s Cognitive Examination-Revised, which also incorporates the Mini-Mental State Examination, providing a double score [35], and for the presence of psychopathology using the Geriatric Depression Scale-30 [36,37]. Participants with objective cognitive deficits (according to the available norms) are excluded.

A comprehensive neuropsychological assessment protocol for detailed neurocognitive performance is performed for eligible participants with 4 tests from the Cambridge Neuropsychological Testing Automated Battery Connect Research system: Motor Screening Task, Rapid Visual Information Processing, Multitasking test, and Spatial Working Memory, and the Auditory Verbal Learning Test [38]. This enabled an in-depth characterization of cognitive function, including measures of attention, visual perception, processing speed, verbal learning, memory, and executive functions, particularly working memory and inhibitory control. Lifestyle habits are screened with the Lifestyle Assessment Toolkit [39]. Physical activity habits are assessed with the International Physical Activity Questionnaire-Short Form [40].

The dementia risk score Lifestyle for Brain Health [41] is applied only at baseline to examine the presence of modifiable risk factors for dementia and, together with the measures International Physical Activity Questionnaire-Short Form, Geriatric Depression Scale, and the Lifestyle Assessment Toolkit, is used to examine potential moderators of program efficacy.

**Table T3:** **Table 3**. List of neuropsychological assessment measures used.

Number	Neuropsychological assessment protocol	Baseline	Postintervention
1	Informed consent and semistructured interview	✓	
2	Hand and eye laterality tests	✓	
3	Addenbrooke’s Cognitive Examination-Revised test	✓	✓
4	Geriatric Depression Scale	✓	✓
5	CANTAB^a^—Motor Screening Task	✓	✓
6	CANTAB—Rapid Visual Information Processing	✓	✓
7	CANTAB—Multitasking Test	✓	✓
8	CANTAB—Spatial Working Memory	✓	✓
9	Auditory Verbal Learning Test	✓	✓
10	Lifestyle for Brain Health (dementia risk score)	✓	
11	Reduced version of the Healthy Lifestyles Assessment Kit	✓	✓
12	International Physical Activity Questionnaire Portuguese Version (short)	✓	✓
13	Auditory Verbal Learning Test—long-term recall	✓	✓

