### Statistical Analysis Plan

The study of the effect of the Activ4Brain program on the primary outcome (cognitive function) is confirmatory because we hypothesize, according to previous evidence, that the integrated cognitive-aerobic training program results in larger improvements than AE alone or no intervention (passive control) [47]. All other analyses are exploratory.

Continuous cognitive outcomes will be summarized descriptively with mean (SD) for each group and time. These variables will be analyzed with repeated-measures ANOVA with 1 between-subjects factor (group) and 1 within-subjects factor (time=preintervention vs postintervention). The Activ4Brain intervention will be considered effective in improving cognitive function if the group × time interaction is significant at a level of .05, if the post hoc tests (with CI adjustment using Bonferroni) show a significant effect of time for the Activ4Brain group, and the improvement is higher for this group than for the other control groups. If the data do not meet assumptions of sphericity, the Greenhouse-Geisser correction will be used. Description of the effect sizes by partial η^2^ will follow the following cutoff points: less than 0.06 will be considered a small effect; between 0.06 and 0.14 will be considered a medium effect; and higher than 0.14 will be considered a large effect [48].

Missing data will be assessed prior to analysis. Analyses will be conducted using the available data (complete case analysis), and participants with missing data for a specific outcome variable will be excluded only from the relevant analysis.

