The retrospective nature of the publication of this protocol has the objective of providing a detailed description of the methods, ensuring that the information is available for trial replication. However, due to the inherent limitation associated with the fact that the publication of the protocol occurred after the end of data collection and the analysis plans presented were not specified before the data were acquired, the results from the study will be used mainly to generate new hypotheses for future clinical trials. Nevertheless, we expect that integrated cognitive and AE will have a stronger effect on cognition than AE alone [47], and we will treat this analysis as confirmatory. However, it is important to note that we are studying the effects of a novel intervention designed specifically for this study, and we do not have strong convictions regarding which specific cognitive domains will be most affected and which cognitive tests will best capture these effects, particularly when addressing cognitive decline in healthy older people. In fact, a large percentage of studies investigating the impact of this type of intervention on cognition use measures of global cognition such as the Mini-Mental State Examination or the Montreal Cognitive Assessment. These tests, while adequate to help diagnose mild cognitive impairment and dementia, suffer from ceiling effects in the cognitively healthy population [62]. To avoid this problem, this protocol includes measures of cognition more sensitive to subtle changes in cognitively healthy older adults.

Notably, it is possible that this type of intervention might be particularly effective in people with lower physical function and/or lower cognitive function who present a higher potential for improvement. In fact, there is evidence that age-related cognitive decline shows high variability, with some individuals aging better than others [63]. Future studies should explore the impact of the intervention focusing on populations with sedentary lifestyles, lower education levels, or poorer cognitive function.

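### Five cognitive domains are primary and the result is called confirmatory, but no rule says how the separate .05 tests combine, so the plan does not control the error rate of the claim at 5%

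*Protocol article*

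**What the plan says.** All from the protocol article.

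- **Primary Outcomes.** The focus is on "measures from the cognitive assessment protocol associated with 5 cognitive domains: executive function, working memory, episodic memory, sustained attention, and processing speed", and the section then designates all five domains as primary. No score is assigned to any domain.
- **Cognitive Assessment.** The detailed battery is four CANTAB tests and one verbal learning test: "Motor Screening Task, Rapid Visual Information Processing, Multitasking test, and Spatial Working Memory, and the Auditory Verbal Learning Test". Which scores stand for which domain is not stated.
- **Statistical Analysis Plan.** On the continuous cognitive outcomes: "These variables will be analyzed with repeated-measures ANOVA with 1 between-subjects factor (group) and 1 within-subjects factor". The programme counts as effective "if the group × time interaction is significant at a level of .05". Two further conditions apply: a Bonferroni-adjusted post hoc test must find a change over time within Activ4Brain, and that group must improve more than the controls. Bonferroni is mentioned only for the post hoc tests.
- **Confirmatory status.** The Statistical Analysis Plan section and the Discussion both call this analysis confirmatory. They and Assessment Procedures speak of cognitive function as one primary outcome, whereas Primary Outcomes lists five domains.
- **Discussion.** The authors write that "we do not have strong convictions regarding which specific cognitive domains will be most affected and which cognitive tests will best capture these effects". They also say that the analysis plans were not specified before the data were acquired, and that the results will mainly serve to generate hypotheses.
- **Sample size.** Sixty-six participants, from one group-by-time interaction test at an undivided alpha of 0.05.

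**The concern.** A confirmatory claim about cognition needs a rule that turns several primary results into one conclusion. Here there are at least five primary tests, each at .05, with no adjustment across them, no hierarchy and no composite. As written, one score that meets the three conditions could support the general claim.

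The setting makes this matter more. The trial is unblinded, data collection ended in April 2025, the Results section says analyses are under way, and the authors have no firm view on which domain or test will show the effect. With the measures still open, the choice of measure could follow the data, and a reader could not tell from this document whether it had.

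**Working it through.** **1. The plan's own figure.** Inputs from the sample size paragraph: f = 0.25, alpha 0.05, power 0.95, 3 groups, m = 2 measurements. The pre-post correlation ρ is not given; 0.5 is assumed.

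λ = f²·N·m/(1−ρ) = 0.0625 × 66 × 2 / 0.5 = 16.5, with 2 and 63 degrees of freedom. Power is 95.3% (N = 63 gives 94.4%). So 66 reproduces, as the size for a single interaction test at .05. Dropout: 66/0.9 = 73.3, hence 74, or 75 as a multiple of three.

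**2. At least one significant interaction, no effect anywhere.**

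- Five independent measures: 1 − 0.95⁵ = 22.6%.
- Five measures, by simulation: about 21% at an assumed correlation of 0.3 and about 19% at 0.5.
- Fifteen independent measures (an assumed number): 1 − 0.95¹⁵ = 53.7%.

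**3. The full three-part rule, no effect, any of five measures.** Change scores were simulated with 22 per arm and correlations between measures of 0 to 0.5. The document leaves two things open: whether the larger improvement must be significant or only numerical, and how the Bonferroni adjustment applies to the time effect. The practice gain, in SD of change and equal in all arms, is assumed.

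| Third condition read as | Practice gain | Rate |
|---|---|---|
| Bonferroni-significant against both controls | none or 0.5 SD | about 0.5% |
| Numerically larger | none; time test Bonferroni-adjusted for three arms | about 2% |
| Numerically larger | none; time test unadjusted | 3–4% |
| Numerically larger | 0.5 SD or more | about 7–8% |

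The upper end can be checked by hand. If a practice gain makes the time condition almost certain, a significant interaction counts only when Activ4Brain ranks first of three arms. By symmetry the rate per measure is then .05/3, and 1 − (1 − .05/3)⁵ = 8.1%.

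With an assumed 15 measures and the numerical reading, the rate is about 8–22%; the top is 1 − (1 − .05/3)¹⁵ = 22.3%. The bottom uses an unadjusted time test and no practice gain. With the adjusted time test and no practice gain, the simulated rate per measure is 0.41%, and 1 − (1 − 0.0041)¹⁵ = 6.0% for independent measures.

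**4. Power cost of Holm.** The first of five steps is at .05/5 = .01. At N = 66 and the planning effect, for the omnibus interaction:

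| ρ (assumed) | λ | Power at .05 | Power at .01 |
|---|---|---|---|
| 0.3 | 11.8 | 86% | 67% |
| 0.5 | 16.5 | 95% | 85% |
| 0.7 | 27.5 | 99.8% | 98% |

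**The case against.** Four counter-arguments deserve weight.

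- **The rule has three parts.** A reader might infer from 23% or 54% that this is how often the trial would falsely claim effectiveness. The document does not support that: a significant interaction alone is not success. On the stricter reading of the third condition the rate is well below 5%. This stands, and it limits the point to a rate that the plan leaves undetermined. It does not show that the rate exceeds 5%.
- **The pool of measures is bounded.** It comes from five named domains and a short battery that includes a motor screening task. Fifteen scores is an assumption, and the text gives no count. This stands too.
- **An article may leave individual scores to a fuller plan.** That is fair for the naming of scores. It does not cover the missing rule across domains, because the article has its own analysis-plan section with an explicit success criterion.
- **The Discussion already lowers expectations.** It admits that the plans came after the data and that the results mainly generate hypotheses. This is real mitigation, but the same paragraph keeps the confirmatory label for the cognitive analysis.

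If all five domains had to succeed, no adjustment would be needed, but the document does not say so. The Bonferroni step works within one outcome and does not answer the point.

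**Conclusion.** The point holds in this form: five primary domains without fixed measures, a .05 test per outcome, no decision rule across outcomes, and a confirmatory label. The plan does not control the error rate of its effectiveness claim at 5%. With five measures and no effect, the full rule gives about 0.5%, 2–4% or 7–8% according to readings that the text leaves open. With an assumed 15 measures on the numerical reading it is about 8–22%. These figures rest on assumed correlations between measures, an assumed practice gain and 22 analysed per arm. A practice gain is plausible, since the passive arm is there to control for retest effects.

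Two stronger inferences are not supported. The sample size is not miscalculated: 66 reproduces, but for one test. Nor does anything in the document show that a measure has been chosen after seeing results; it only leaves that possible. What happens when aerobic exercise alone works is a matter of the comparator condition and is not counted here.

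This should be settled before results are reported, because it governs the trial's only confirmatory claim.

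**What to change.** Name one measure for each of the five domains now, and state what by-arm data have already been seen. Then choose one of the following:

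1. Make a single composite, the mean of the five baseline-standardised domain scores, the primary outcome at .05, with the domains as supportive.
2. Apply Holm across the five domain interaction tests, and confine any confirmatory claim to the domains that are rejected.

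Label all other CANTAB and verbal learning scores exploratory. If by-arm results have already been seen, drop the confirmatory label, which fits the Discussion's own statement about generating hypotheses.

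**Cost.** The change itself is wording. Under Holm, omnibus power at N = 66 falls from 95% to about 85% at the first step if the pre-post correlation is 0.5; at .01 it is 67% for a correlation of 0.3 and 98% for 0.7. A composite avoids that loss but may dilute an effect confined to one domain. Dropping the label gives up the confirmatory claim.

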#### Secondary Outcomes

Secondary outcomes include:

Evaluation of the impact of the Activ4Brain program on brain and autonomic function and physical health markers, including molecular changes associated with inflammation and neuroprotection, and investigation of potential moderators of the program’s efficacyEvaluation of participants’ adherence and retention through attendance rates across all intervention sessions and participation trends over timeEvaluation of the feasibility of the Activ4Brain program, including its acceptability, accessibility, and usability

#### Other Outcomes

Other outcomes include evaluation of changes in:

Cardiovascular and physical functional fitness and body composition, which are important for preventing chronic diseases and age-related muscle loss and are associated with cognitionPhysical activity participation, which is especially important in older people who have a sedentary lifestyle;Psychosocial measures and quality of life to investigate if our group-based intervention positively influences the mental health and emotional well-being of the participants, for example, by reducing loneliness and isolation.

### Statistical Analysis Plan

The study of the effect of the Activ4Brain program on the primary outcome (cognitive function) is confirmatory because we hypothesize, according to previous evidence, that the integrated cognitive-aerobic training program results in larger improvements than AE alone or no intervention (passive control) [47]. All other analyses are exploratory.

Continuous cognitive outcomes will be summarized descriptively with mean (SD) for each group and time. These variables will be analyzed with repeated-measures ANOVA with 1 between-subjects factor (group) and 1 within-subjects factor (time=preintervention vs postintervention). The Activ4Brain intervention will be considered effective in improving cognitive function if the group × time interaction is significant at a level of .05, if the post hoc tests (with CI adjustment using Bonferroni) show a significant effect of time for the Activ4Brain group, and the improvement is higher for this group than for the other control groups. If the data do not meet assumptions of sphericity, the Greenhouse-Geisser correction will be used. Description of the effect sizes by partial η^2^ will follow the following cutoff points: less than 0.06 will be considered a small effect; between 0.06 and 0.14 will be considered a medium effect; and higher than 0.14 will be considered a large effect [48].

Missing data will be assessed prior to analysis. Analyses will be conducted using the available data (complete case analysis), and participants with missing data for a specific outcome variable will be excluded only from the relevant analysis.

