### Participant Recruitment, Eligibility Criteria, and Sample Size

Participants are recruited from Portugal’s Coimbra District through personal communications, press releases, social media posts, and distribution of informative leaflets and posters. Recruited participants receive comprehensive information regarding data collection procedures, exercise protocols, and measures of protection of personal information procedures. Participants who volunteer to participate in the study are interviewed for eligibility and asked to sign an informed consent form.

Inclusion criteria are cognitively healthy men and women between 55 and 75 years of age, with a physical condition compatible with the practice of moderate AE. Exclusion criteria include any disability or health problem incompatible with moderate AE and objective cognitive impairment. The Physical Activity Readiness Questionnaire is used to screen contraindications for physical exercise. Before the intervention, we ensure participants’ fall risk is low using the Timed Up and Go (TUG) test [25].

Participants are instructed to continue any ongoing concomitant care. Details of the concomitant care received are recorded at baseline and, to assess any changes, at follow-up.

Sample size determination has been made using the G*power (version 3.1.9.7; written by Franz Faul, Universität Kiel, Germany) program. As reported in previous studies [26,27], we expect a small to moderate effect size of the Activ4Brain program on cognitive function (our primary end point). We calculated a sample size of 66 participants by setting Type I error (α) at 0.05, Type II error rate (1−β) at 0.95, and an effect size η^2^ of 0.06 (corresponding to an effect size *f* of 0.25, using the option for effect size specification as in G*Power 3.0) for repeated-measures ANOVA, within-between interaction, with 3 groups and 2 repeated measures. Accepting a dropout rate of 10%, 75 participants are recruited.

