### Randomization and Blinding

This trial is a quasi-randomized controlled unblinded trial. After recruitment, participants are assigned to 1 of 3 groups based on sex and age, ensuring that each group has similar sex ratios and age ranges. These balanced groups are then randomly assigned, using the random permutation of integers function from MATLAB (The MathWorks Company Ltd), to 1 of the 3 interventions: Activ4Brain, AE, or control.

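### The primary analysis is a change-score comparison without covariates: valid, but less precise than adjusting for the baseline score, and open to chance baseline imbalance

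*Protocol article*

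**What the plan says.** The Statistical Analysis Plan section states the model for the cognitive outcomes: "These variables will be analyzed with repeated-measures ANOVA with 1 between-subjects factor (group) and 1 within-subjects factor". The within-subject factor has two levels, before and after the intervention. The programme counts as effective "if the group × time interaction is significant at a level of .05", provided also that Bonferroni-adjusted post hoc tests show a time effect within the Activ4Brain group and that this group improves more than the controls. Neither the baseline score, age nor sex enters the model. Moderators of efficacy are mentioned elsewhere, but only as secondary, exploratory work.

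The Randomization and Blinding section says that "participants are assigned to 1 of 3 groups based on sex and age, ensuring that each group has similar sex ratios and age ranges". The three assembled groups are then randomly permuted to the three interventions. The sample size section uses the same unadjusted model.

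**The concern.** A group-by-time test on two occasions compares mean change between arms. Change scores subtract the whole baseline value, whereas the data usually support a slope below 1. Two things follow. Residual variance is larger than it need be, so intervals are wider. And when arms differ at baseline, part of that difference returns in the effect estimate as regression to the mean. The arms have about 24 participants each (73 enrolled / 3 = 24.3), and the allocation balances sex and age but not baseline cognition. Both effects can therefore be of practical size, and the data needed to avoid them are already collected.

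**Working it through.** **Inputs.** From the sample size section: "We calculated a sample size of 66 participants"; "setting Type I error (α) at 0.05"; power "at 0.95, and an effect size" f = 0.25; "with 3 groups and 2 repeated measures"; "using the option for effect size specification as in G*Power 3.0". From the Results: 73 enrolled. Assumed, because the article does not give them: ρ (0.3 to 0.8) and equal pre and post SDs.

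**1. The plan's own figure.** Under the G*Power 3.0 specification, λ = f²·N·m/(1−ρ), with 2 and N−3 degrees of freedom. At ρ = 0.5 and N = 66, λ = 0.0625 × 66 × 2 / 0.5 = 16.5, and power is 95.3%. The smallest multiple of three that reaches 95% is 66, so the stated number reproduces. For dropout, 66/0.9 = 73.3, or 74 rounded up, and 75 is the next multiple of three.

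**2. Equivalence.** With two occasions the interaction F test is the one-way ANOVA of post minus pre.

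**3. Precision.** Let σ² be the common variance.
- Change score: Var = 2(1−ρ)σ².
- ANCOVA residual: Var = (1−ρ²)σ².
- Ratio: (1+ρ)/2, which is 0.75, 0.85 and 0.90 at ρ = 0.5, 0.7 and 0.8. Simulation (20,000 runs, 22 per arm) gave 0.76, 0.86 and 0.92.
- At ρ = 0.5, 66 participants analysed by ANCOVA work like 66/0.75 = 88 analysed by change scores; at ρ = 0.7, like 66/0.85 ≈ 78.

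If the SDs differ, the advantage is (1−β)² times the baseline variance, where β = ρ × (post SD/pre SD). It vanishes when β = 1. For example, with ρ = 0.8 and a post SD 1.25 times the pre SD, both variances are 0.5625 in units of the baseline variance.

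**4. Power and sample size.** Dividing λ by the ratio and removing one degree of freedom gives λ = 16.5/0.75 = 22 at ρ = 0.5.

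| ρ | Power at 66, change → ANCOVA | N for 95% power, change → ANCOVA |
|---|---|---|
| 0.3 | 86.0% → 96.9% | 90 → 60 |
| 0.5 | 95.3% → 98.9% | 66 → 51 |
| 0.6 | 98.4% → 99.6% | 54 → 45 |
| 0.7 | 99.8% → 99.9% | 42 → 36 |
| 0.8 | about 100% for both | 30 → 27 |

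The gain matters more for a smaller true effect. At ρ = 0.5, an effect that the planned model detects with 80% power at N = 66 (f about 0.196) is detected by ANCOVA with about 90%.

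**5. Baseline imbalance.** Under simple random allocation with 24 per arm, the baseline difference between two arms has an SD of √(2/24) = 0.289 outcome SDs. Given a difference d, the change-score contrast shifts by −(1−ρ)d:
- ρ = 0.5: 0.5 × 0.289 = 0.14 SD.
- ρ = 0.7: 0.3 × 0.289 = 0.09 SD.

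In the simulation, a baseline difference of 0.30 SD shifted the change-score contrast by −0.15 (ρ = 0.5) and −0.09 (ρ = 0.7). The ANCOVA contrast moved by less than 0.01 SD.

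**The case against.** The strongest reply is that this is a preference and not an error. The planned test is valid, its type I error is unaffected by this choice, and the sample size was computed for that same model and reproduces. All of that stands. So do several limits:

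- A reader might infer that the model ignores the baseline score. It does not. It subtracts it with a slope fixed at 1; what is missing is an estimated slope.
- A reader might infer a biased estimate. Averaged over random allocations, the change-score contrast is unbiased; the shift is conditional on an observed imbalance.
- The 0.289 SD assumes simple random allocation of individuals. Balancing on age and sex would reduce it to the extent that they predict cognition. Where allocation is truly non-random, ANCOVA is not automatically less biased than change scores. The quasi-randomised design is therefore not in itself an argument for the switch.
- A reader might infer that leaving out age and sex costs much. The groups were built to be similar on both, constant additive effects cancel in a change score, and the article gives no figure from which a gain could be computed.
- The trial is unblinded and data collection is over, so replacing the confirmatory model now has a cost in credibility.

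The timing objection does not defeat the change. The article says that analyses are ongoing and already concedes that its analysis plans were not specified before the data were acquired. The planned ANOVA can be kept and reported alongside.

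**Conclusion.** The point holds as one of efficiency and robustness. The plan fixes a valid but less precise primary model, when baseline adjustment is available at almost no cost. With equal SDs, the variance falls by 25%, 15% and 10% at ρ = 0.5, 0.7 and 0.8. At the planned effect and ρ = 0.5, power rises from 95.3% to 98.9%. The gain shrinks as ρ approaches 1 and can vanish if the SDs differ. Conditional on a typical chance imbalance, adjustment removes a shift of roughly 0.09 to 0.14 SD.

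A reader might go further and infer that the trial is underpowered because of this choice. Reading 0.06 as a partial η² for the interaction gives λ = 66 × 0.06/0.94 = 4.21, with power of about 42% for the planned model and 53% for ANCOVA at ρ = 0.5. The article does not support using those figures here. They set aside the G*Power 3.0 specification that it names, yet borrow the ρ of 0.5 that only that specification implies. How the effect size was specified is a separate question.

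**What to change.** Make the primary between-arm comparison an ANCOVA of the post-intervention score on arm, adjusted for the baseline score, or an equivalent baseline-constrained mixed model. Add age and sex because they were used to form the groups, without claiming a computed gain for them. Report adjusted pairwise differences with 95% CIs.

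Restate the success rule to fit: the overall arm effect in place of the interaction, and adjusted contrasts of Activ4Brain against each control. ANCOVA does not supply the within-group time effect that the present rule requires, so report that as a separate model-based estimate for the Activ4Brain group.

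Keep the repeated-measures ANOVA as a sensitivity analysis. Date the change and disclose that it was made after data collection.

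The cost is three degrees of freedom (baseline score, age as a linear term, sex) and a documented change of plan after data collection. No new data are needed.

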**Figure 1. F1:**
[figure not shown]
Study flowchart. The research protocol is divided into 3 main parts. Part 1, with a duration of 1 month, corresponds to the initial data collection phase (T0), serving as the baseline assessment. Part 2 corresponds to the 3-month intervention protocol, which includes the Activ4Brain program (Activ4Brain group) and the aerobic exercise-only program (AE group). Part 3, with a duration of 1 month, corresponds to the follow-up data collection phase (T1) conducted after the intervention.

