## Results

Data collection started in January 2024 and finished in April 2025. Seventy-three individuals (40 women and 33 men) were enrolled in the study and assigned to the 3 groups. The average age was 66 (SD 6) years. Data analyses are ongoing, with the publication of the results estimated for 2026 and 2027.

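### Data collection ran about 16 months against a 5-month flow, so entry was staggered, yet the confirmatory model has no term for intake wave

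*Protocol article*

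**What the plan says.** The Figure 1 caption gives the flow in three parts. For baseline it says: "Part 1, with a duration of 1 month, corresponds to the initial data collection phase (T0), serving as the baseline assessment". The training programs then take 3 months. For follow-up it says: "Part 3, with a duration of 1 month, corresponds to the follow-up data collection phase (T1) conducted after the intervention". On the calendar, the Results section states: "Data collection started in January 2024 and finished in April 2025".

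Randomization and Blinding describes one procedure. The first step reads: "After recruitment, participants are assigned to 1 of 3 groups based on sex and age". The second step allots whole groups to the interventions: "These balanced groups are then randomly assigned, using the random permutation of integers function from MATLAB". The section mentions no wave, cohort, rolling entry or repeated permutation. Sex and age are the only balancing factors.

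The Statistical Analysis Plan section analyses the continuous cognitive outcomes by "repeated-measures ANOVA with 1 between-subjects factor (group) and 1 within-subjects factor (time=preintervention vs postintervention". It requires the group × time interaction to be significant at .05 and calls the analysis confirmatory. Participants with missing data are dropped outcome by outcome. Adherence Rate and Adverse Events also requires 60% adherence for inclusion in the analyses.

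**The concern.** People who enter together share season, calendar time and whatever changes over the study period. If the three groups were formed and permuted separately at each intake, intake is part of the restricted allocation, and the analysis should normally reflect it. If there was one allocation with staggered starts, the article does not say that start date was balanced between arms.

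The consequence depends on the arm mix within intakes, which is not reported:

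- **Arms balanced within intakes.** A common calendar effect cancels from group × time. Between-intake variance stays in the error term, so the test is conservative and power is forgone.
- **Arm mix differing between intakes.** Part of the difference between intakes enters the arm contrast, and the nominal 5% level is no longer held.

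Balance in the analysed set cannot be taken for granted even if allocation was even. The 73 enrolled do not divide by three. The adherence rule rests on exercise-session attendance, so it can remove people only from the two exercise arms. Complete-case exclusion then acts separately on each outcome.

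**Working it through.** **The plan's own figure.** For the within-between interaction with the effect size the article specifies, λ = N·m·f²/(1−ρ), with N = 66, m = 2, f = 0.25. The correlation ρ is not stated; 0.5 is assumed. Then λ = 66 × 2 × 0.0625 / 0.5 = 16.5 on 2 and 63 degrees of freedom, and power is 0.953. The stated 66 is reproduced. Dropout: 66/0.9 = 73.3, so 74, or 75 in three equal arms, as stated. No allowance for waves enters this calculation.

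**Timeline.** 1 + 3 + 1 = 5 months per pass. January 2024 to April 2025 is 12 + 4 = 16 calendar months. 16/5 = 3.2, so one simultaneous pass does not fill the period, and three consecutive passes would fit.

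**Effect of leaving wave out.** With two time points, the group × time test equals a one-way F test on change scores, so change scores were simulated. Assumed: 72 participants in three waves of 24, with wave explaining 5% to 20% of change variance. *Balanced* means 8 per arm in each wave. *Uneven* means 12/6/6, with the larger arm rotating over the waves.

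| Arm mix | Type I error, group and time only (wave share 5% to 20%) | With wave |
|---|---|---|
| Balanced | 4.2% down to 2.5% | about 5% |
| Uneven, 12/6/6 | 5.6% up to 7.7% | about 5% |

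A separate run with 40,000 trials per setting drew wave effects at random, with SD 0.25, 0.5 or 1.0 of the within-wave SD of change. The corresponding variance shares, s²/(1+s²), are 0.0625/1.0625 = 5.9%, 0.25/1.25 = 20% and 1/2 = 50%. Without wave, type I error was 4.3%, 3.3% and 1.7% for the balanced mix and 5.7%, 7.1% and 9.9% for the uneven mix. It was about 5% throughout with wave. With fixed wave effects at shares of 5%, 10% and 20%, the uneven mix gave 6.1%, 6.9% and 8.5%. The upper end at a 20% share therefore lies between about 7% and 8.5%, depending on how wave effects are modelled.

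**Power, balanced arms.** Pairwise Activ4Brain versus AE contrast, assumed difference 0.8 SD, total variance held constant:

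| Wave share of change variance | Without wave | With wave |
|---|---|---|
| 0% | 78.2% | 78.0% |
| 5% | 78.5% | 79.7% |
| 10% | 79.3% | 82.3% |
| 20% | 80.4% | 86.1% |

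The gains are 1.2, 3.0 and 5.7 points at shares of 5%, 10% and 20%. The first row is the cost if wave explains nothing.

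**Shift in the contrast.** Shift = (difference between two arms in the share of participants in a wave) × (that wave's difference in change from the rest). If arms differ by one person of 24, the shift is 1/24 × 0.3 to 0.5 SD = about 0.01 to 0.02 SD. If one arm has 45% of its people in a wave and another 25%, it is 0.20 × 0.3 to 0.5 SD = 0.06 to 0.10 SD.

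**What a wave term does not reach.** If each arm-by-wave group of 8 shares its own effect, with intraclass correlation 0.01, 0.05 or 0.10, type I error is 6.0%, 10.8% and 17.4% without a wave term and 6.0%, 11.0% and 18.1% with one.

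**The case against.** The strongest reply is that intake batches are nowhere documented. The article describes one allocation procedure and says 73 people were assigned to three groups. Classes hold 4, so a single allocation with staggered class starts, or rolling entry, would also fill 16 months. This stands as far as it goes. A reader might infer that allocation must have run in batches, but the documents support only staggered entry; repeated allocation is probable, not stated.

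A reader might also infer that the trial has no protection from calendar effects. That does not follow. If the three groups were formed 1:1:1 at each intake, all arms ran concurrently and a common seasonal effect cancels from the group × time contrast. The passive control then does its job across the whole trial.

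Nor do the documents support a bias of 0.06 to 0.10 SD. It needs an arm imbalance of about 11 against 6 of 24 in one wave. That is not reported, and 1:1:1 formation per wave would largely prevent it.

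It can further be said that a blocking term is an efficiency refinement commonly left to a full analysis plan. That would carry weight if the article were silent on the model. Instead it states the number of factors for an analysis it calls confirmatory. Finally, the clustering that could inflate error most is not cured by a wave term. That is correct, and it is a separate issue.

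**Conclusion.** The point holds in a limited form. Staggered entry follows from the article's own dates, and the stated model takes no account of it. With arms balanced within intakes, the harm is a conservative test (about 4.2% down to 2.5% instead of 5%) and a forgone gain of roughly 1 to 6 power points, with no bias. With an uneven mix of the 12/6/6 kind, type I error is about 5.6% to 7.7%, and a calendar or season difference enters the arm contrast. A wave term restores about 5% in both cases.

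Three waves, a wave share of 5% to 20% and the arm mix are all assumptions; the article gives none of them. The change is worth making because it is cheap, analyses are still ongoing, and the Discussion concedes that the analysis plan was not specified before the data were acquired.

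**What to change.** In Randomization and Blinding, state whether group formation and permutation were done once or repeated, the number of intake waves, and the number per arm in each wave, both as allocated and as analysed.

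In the Statistical Analysis Plan section, add intake wave as a fixed between-subjects factor with wave × time, or wave as a covariate in the equivalent change or baseline-adjusted model. Define wave as the set of recruits among whom the three groups were formed or, if there was a single allocation, as entry period. Take it from allocation records and entry dates, and fix the definition before looking at outcomes by arm. Base the post hoc arm comparisons on the same model.

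The cost is about 2 degrees of freedom with three waves: power moves from 78.2% to 78.0% if wave explains nothing. No new data should be needed, since entry dates should already be on file. If the counts show that arms ran in different waves, wave and arm are confounded and this term cannot separate them; the report should then say so. Clustering in classes of 4 and shared arm-by-wave effects need their own treatment.
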